Besides the effectiveness of the injectables, the hypothesis is that the needle is used to either break up scars or poke holes in the injured tendon so that bleeding occurs. The blood cells carry precursors, which eventually develop into collagen to replace the damaged tendon. Therefore, this study compares the different injectables with perforation without application of an injectable.

The current debate on studies related to injectables for LE is that in most cases the perforations are performed manually and ‘blindly’ without ultrasound guidance. Moreover, the number and depth of perforations is often not defined. Proper comparison of injectables for LE is therefore questionable [7]. The proposed study compares the effectiveness of perforation of the Extensor Carpi Radialis Brevis (ECRB) tendon to perforation with application of autologous blood or dextrose in the treatment of LE in a standardized and ultra-sound guided way. This overcomes bias due to manually performed injection therapy.

Our hypothesis is that there is no difference in effectiveness between perforation only and perforation with application of one of the injection fluids. The potential health care efficiency gain consists of more homogeneity in the treatment of LE. Hereby, unnecessary treatments can be avoided, a more universal method of treatment can be established and the quality of the treatment can be improved.

The primary objective of this study is to compare the difference in effectiveness of perforation only versus perforation with application of autologous blood or dextrose on pain in the treatment of LE. The primary endpoint is pain on the lateral side of the elbow after a provocation test 5 months after treatment. The secondary objectives are to examine quality of life and functional recovery.

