#### Primary outcome

The main outcome measures are the changes in pain using a Visual Analog Scale (VAS, 0–100) [9]. The VAS consists of a 100-mm horizontal numbered line anchored at one end (0) with the words “no pain” and at the other end (100) with the words “worst pain imaginable.” Patients are asked to score their pain on this line during rest (at time of measure), provocation and maximum grip strength. The provocation test is conducted on the outpatient clinic by resisted dorsiflexion of the wrist during full elbow extension. The VAS pain scores will be measured at baseline and 8 weeks, 5 months and 1 year after treatment.

The main outcome measure is the change in VAS when performing the provocation test 5 months after treatment.

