### Sample size and power calculation

A reduction in pain of at least 10 mm on a 0–100 mm visual analogue scale is deemed a clinical significant improvement. Due to the three study arms of our RCT, there are also three null hypotheses tested:| A - B | ≥ 10 | A - C | ≥ 10 and | B - C | ≥ 10 points on the VAS pain scale, according to a superiority design. In which A, B and C stands for dextrose, autologous blood and perforation only respectively. A number of 47 patients is required in each trial arm when a two-sided 98% confidence interval is used, with a two-sided alpha of 2%, corresponding to a z-value of 2.34 (J Scott Armstrong: Tables for Statistical Significance with Multiple Comparions). To adjust for a maximum of 10% dropout over the one year follow up period, 55 patients will be included in each of the three trial arms. Therefore, a total of 165 patients are needed. It is expected that each week in both hospitals a total of 3 patients can be included. Therefore, the inclusion period takes about 55 weeks. Patients that are withdrawn from the study will not be replaced, since there is accounted for these dropouts in the power analysis.

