To get a better understanding, a linear mixed model analysis will be performed with the three repeated measurements of pain VAS as dependent variables. Along with treatment (a three-level nominal variable) the following covariables will be included in the model as independent variables: baseline pain VAS, the binary variable perceived aggravation of pain due to work ((totally) agree vs otherwise) and a three-level nominal variable time (visit number). Moreover, the interaction between treatment and time will be tested. If this interaction is not significant at the 0.01 level, then one overall treatment effect will be estimated assuming parallelism of the treatment effect. If this interaction turned out to be significant at the 0.01 level, then the effect of the 5 months’ visit will be considered the main effect of interest. Effects will be quantified by estimating two-sided 98% confidence intervals of the pair wise mean differences in pain VAS between the three treatment groups. Equivalence between two treatments is accepted if such a confidence interval is totally overlapped by the interval − 10 + 10. A restricted maximum likelihood estimation method will be used to estimate the coefficients so that missing values are properly imputed in order to meet the itt-condition. Under the pp-condition only patients with non-missing observations will enter the linear mixed model.

Similar analysis will be performed for functional recovery and quality of life. Otherwise the descriptives of the secondary outcome measures will be reported for the three groups.

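### The primary endpoint is fixed at 5 months, but an interaction pre-test at 0.01 decides whether the 5-month contrast or one effect over three visits becomes the main effect

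*Protocol article*

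**What the plan says.** Two sections of the protocol article fix the endpoint. The last paragraph of Background states: "The primary endpoint is pain on the lateral side of the elbow after a provocation test 5 months after treatment". Primary outcome repeats it: "The main outcome measure is the change in VAS when performing the provocation test 5 months after treatment". Neither attaches a condition.

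The second part of Statistical analysis describes the model: "a linear mixed model analysis will be performed with the three repeated measurements of pain VAS as dependent variables". The covariates are baseline VAS, work-related aggravation and visit. Treatment by time is tested, and the result chooses between two branches:

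- **Not significant:** "If this interaction is not significant at the 0.01 level, then one overall treatment effect will be estimated assuming parallelism of the treatment effect".
- **Significant at 0.01:** "then the effect of the 5 months’ visit will be considered the main effect of interest".

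Pairwise 98% intervals are then computed, and two treatments are accepted as equivalent if the interval lies wholly within −10 to +10.

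Under Crossover, perforation-only patients who are not a success at 5 months are to receive autologous blood as well. The 1-year score in that arm can therefore follow a second treatment.

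**The concern.** The data choose what the trial estimates. A non-significant result at 0.01 is not evidence that the treatment differences are the same at each visit, and so strict a level makes a miss more likely. The reported 98% interval takes no account of the selection step.

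The article itself gives a reason to expect differences that vary by visit. The crossover can change the 1-year contrast against perforation only. In addition, the 1-year contact is by email or telephone (Secondary outcomes), while the provocation test is done in the clinic (Primary outcome), so the third score may not be the same measurement.

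The direction matters as well. The investigators' stated hypothesis is no difference, and under an equivalence rule a diluted effect favours that conclusion.

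**Working it through.** **1. The plan's own figures.** The 47 per arm cannot be reproduced or refuted, because the article gives neither SD nor power. At 80 to 90% power it would imply an SD of about 15.3 to 13.4 for superiority, or 13.4 to 12.2 for equivalence at zero difference. The z-value of 2.34 agrees with a three-group Tukey value (2.344); a plain two-sided 2% gives 2.326.

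**2. Inputs.**
- From the article: three arms, three follow-up visits, 55 randomised per arm with 10% dropout (55 × 0.9 = 49.5, taken as 50), pre-test level 0.01, z = 2.34, margin 10 mm.
- Assumed: SD 15 to 25, equal correlation of 0.4 to 0.6 between visits, complete data, no baseline covariate in the simulation, and one arm differing from the other two by 4, 12 and 4 mm at 8 weeks, 5 months and 1 year.

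**3. How often the pre-test misses.** The visit average of the differences is (4 + 12 + 4)/3 = 6.67. Deviations from it are −2.67, 5.33 and −2.67, with sum of squares 42.67. With one of three arms differing, the interaction sum of squares is 42.67 × 2/3 = 28.44.

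Non-centrality = n × 28.44 / [SD² × (1 − correlation)], with 4 and 2 × (150 − 3) = 294 degrees of freedom. For SD 20 and correlation 0.4 this is 50 × 28.44 / (400 × 0.6) = 5.93, which gives power 0.234.

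| SD | Correlation | Power at 0.01 | Overall effect used |
|---|---|---|---|
| 15 | 0.4 | 0.504 | 50% |
| 15 | 0.6 | 0.754 | 25% |
| 20 | 0.4 | 0.234 | 77% |
| 20 | 0.6 | 0.408 | 59% |
| 25 | 0.4 | 0.125 | 88% |
| 25 | 0.6 | 0.221 | 78% |

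**4. Consequence for the 5-month effect.** The two-step rule was simulated over the same range.

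| | Pre-test rule | 5-month contrast fixed |
|---|---|---|
| Nominal 98% interval covers 12 mm | about 74 to 89% | about 98% |
| Equivalence within ±10 wrongly accepted | about 1 to 10% | at most 0.2% |

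A small SD does not remove the problem. The lowest coverage occurs at SD 15 with correlation 0.4: the pre-test misses less often there, but the narrower interval around the average excludes 12 mm more often.

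**5. When effects are parallel.** With no true difference at any visit, the overall effect is used in 99% of trials by construction, and simulated coverage stays at about 98%.

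**6. Interval widths.** Half-width at 5 months = 2.34 × SD × √(2/50) = 0.468 × SD, which is 7.0, 9.4 and 11.7 mm at SD 15, 20 and 25. For the visit average this is multiplied by √[(1 + 2 × correlation)/3], that is 0.775 at 0.4 and 0.856 at 0.6. The 5-month interval is therefore 1/0.856 = 1.17 to 1/0.775 = 1.29 times as wide.

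**The case against.** **The model may be only supportive.** It is introduced with "To get a better understanding, a linear mixed model analysis will be performed". The preceding paragraphs list pairwise t-tests, a primary aim and a 98% interval. With the unconditional endpoint statement, a reader could take this as a 5-month comparison with the model in support. The ambiguity is genuine, but it does not settle the matter. Those paragraphs name no time point and also refer to a mixed model. The main effect of interest and the only equivalence decision are defined through the model.

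**The endpoint is usually replaced by another quantity.** A reader might infer this from how often the overall effect is used. The documents do not support it. Under parallel effects, including the article's own hypothesis of no difference, the overall and 5-month effects have the same value. At SD 15 the 4/12/4 profile leads to averaging in only 25 to 50% of trials.

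**A 6.7 mm average lies inside ±10, so equivalence would follow.** This is also tempting, and wrong. The rule needs the whole interval inside the margin. At SD 20 to 25 the average's half-width is about 7.3 to 10.0 mm, so an estimate of 6.7 gives an upper limit of about 14 to 17. The frequency of averaging is not the frequency of a wrong conclusion; the latter is about 1 to 10%.

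**Averaging buys precision.** This stands, and it is a real cost of the change.

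**Conclusion.** The point holds. Background and Primary outcome fix the time point unconditionally, while Statistical analysis makes it depend on a test result and attaches the intervals and the equivalence rule to whichever effect is selected. No section sets a 5-month analysis that stands whatever the pre-test shows.

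The harm is conditional: it needs effects that differ by visit and a pre-test that fails to detect this. The sizes above rest on assumed SDs, correlations and one chosen profile, since the article gives none of these. They show that the loss of coverage can be material, not that it will occur. Because the rule governs the trial's main conclusion and can be corrected in the text, it should be corrected before any unblinded analysis.

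**What to change.** Delete the pre-test. Always keep treatment by time in the mixed model. State that the pairwise 5-month contrasts with 98% intervals are the primary result and the sole basis of the ±10 rule. Report the interaction test and any average over visits as secondary. This changes a few sentences and needs no new data.

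The cost should be stated with the change. The 5-month interval is about 17 to 29% wider than that of the visit average. At an SD of about 25 its half-width of 11.7 mm exceeds the 10 mm margin, so equivalence at 5 months could not then be shown. In simulations with 47 per arm, correlation 0.5 and no true difference, the chance of showing equivalence falls from 89% to 62% at SD 15, from 46% to about 9% at SD 20, and from 6% to zero at SD 25. Adjusting for baseline VAS, as already planned, may reduce the residual SD; by how much cannot be told from the article.

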### Adverse events

Adverse events (AEs) are defined as any undesirable experience occurring to a subject during the study, whether or not considered related to the needle therapy. All adverse events reported spontaneously by the subject or observed by the investigator or his staff will be recorded. The expected side effects are similar to a normal injection, such as temporarily worsening of the symptoms and any additional pain caused by the injection therapy itself. However, these side effects are not specific for this method. The ITEC device mimics the normal treatment of lateral epicondylitis with manual injection therapy performed by an orthopaedic surgeon. A pilot study, performed at the Amphia hospital Breda, the Netherlands, concerning 25 patients treated with perforation therapy with the ITEC device reported no adverse device effects.

All AEs will be monitored until they have abated, or until a stable situation has been reached in which no changes are expected. Depending on the event, follow up may require additional tests or medical procedures as indicated, and/or referral to the general physician or a medical specialist.

Subjects can leave the study at any time for any reason if they wish to do so without any consequences. The investigator can decide to withdraw a subject from the study for urgent medical reasons.

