**Methods/design:**

A multicenter, randomized controlled trial with a superiority design and 12 months follow-up will be conducted in four Dutch hospitals. One hundred sixty five patients will be recruited in the age of 18 to 65 years, with chronic symptomatic lateral epicondylitis lasting longer than 6 weeks, which have concordant pain during physical examination. Patients will be randomized by block randomization to one of the three treatment arms. The treatment will be blinded for patients and outcome assessors. The following three injection therapies are compared: perforation with application of autologous blood, perforation with application of dextrose and perforation only. Injections will be performed ultrasound guided in a standardized and automated way. The primary endpoint is: pain (change in ‘Visual Analogue Scale’). Secondary endpoints are quality of life and functional recovery. These measurements are collected at baseline, 8 weeks, 5 months and 1 year after treatment.

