**Fig. 3 Fig3:**
[figure not shown]
ITEC disposable. Image under copyright by ITEC Medical B.V. (Enschede, the Netherlands) and published with their permission

The perforation of the affected tendon is as follows:Disinfection of the skin of the elbowPositioning of the arm in 90 degrees flexion in the elbow and 90 degrees abduction in the shoulder.Depth measurement of the Extensor Carpi Radialis Brevis tendon with an ultrasound probe (5–12 MHz phased array transducer).Setting the patient specific depth of the perforation on the device.Perforation by a single movement of the arm of the device in which the elbow is infiltrated with one of the injectables.Application of 12 drops of the injection fluid (if applicable), with a total amount of 0.4 cc (by a 2 cc syringe).

Before treatment a venous blood sample will be collected from each patient by a venipuncture from the unaffected arm. This sample is used for the treatment of patients in the autologous blood treatment arm and is covered by opaque tape. For the treatment with dextrose or perforation without infiltration this is redundant, but it will be done in order to ensure blinding. The venous blood sample is collected by a supporting nurse or by the physician who performs the treatment.

Co-interventions as visiting a physiotherapist, acupuncturist or osteopath are allowed and will be registered. The use of pain medication besides the needling therapy is allowed and will be registered. After the injection patients are advised to move their arm as they normally do but to avoid lifting and heavy labor for one week.

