#### Secondary outcomes

Secondary outcome measures are quality of life and functional recovery. Assessments will be made at baseline and 8 weeks, 5 months and 1 year after treatment. For the functional recovery a physical examination is conducted of the affected arm compared to the healthy arm by an orthopaedic surgeon or trained resident. Table 2 shows the items scored at baseline with physical examination. At the 8 weeks and 5 months follow-up visits, a specialized nurse, physiotherapist, trained resident or orthopaedic surgeon (depending on the hospital the patient is treated) will perform a physical examination of both elbows (Table 1). To assess the functional recovery, work ability and patients’ subjective experience on function pain and quality of life the patients are asked to complete a number of questionnaires (Table 2).

**Table 1 Tab1:** Physical examination

Test	Gradation
At baseline	
Valgus stability	Grade 1/2/3
Pivot shift	Positive/negative
Position of the axis	Normal/valgus/varus
Motor function and sensibility of the ulnar nerve	Intact/disturbed
At baseline, 8 weeks and 5 months	
ROM; Flexion/extension, pronation/supination. Measured by classic goniometry	In degrees
Hydrops	Yes/no
Pain on palpation epicondyle and ECRB;	Yes/no
Pain during dorsiflexion of the wrist (from a neutral position and elbow straight) against resistance	Yes/no
Strength; maximum voluntary hand force measured with a Jamar manual force meter [20]	In Kilogram
Strength; ratio between the affected and healthy arm is calculated. Three consecutive measurements will be performed with one minute intervals between contractions.	In Kilogram The average force of three repetitions will be calculated

**Table 2 Tab2:** Overview of questionnaire used to assess the functional recovery, work ability and patients subjective experience on function pain and quality of life. The questionnaires will be completed at baseline, 8 weeks, 5 months and 1 year after treatment

Measures	Questionnaires	Scores	Reliability and validity	Population
Physical function and symptoms	Quick-DASH [10–12]	0 (no disability) to 100 (most severe disability)	Cronbach α > or = 0.92 and an ICC^a^ > or = 0.94. validity was established (r > or = 0.64	Patients with various upper-limb conditions

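### Adverse events are collected by spontaneous report or staff observation and the first planned assessment is at 8 weeks, so short-lived worsening after injection will probably be under-counted in all arms

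*Protocol article*

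**What the plan says.** The Adverse events section of the protocol article defines an adverse event broadly: any unwanted experience counts, whether or not it is thought to be related to treatment. On collection it states: "All adverse events reported spontaneously by the subject or observed by the investigator or his staff will be recorded". Among the expected side effects it lists "temporarily worsening of the symptoms and any additional pain caused by the injection therapy itself". Events, once known, are followed until they resolve or stabilise.

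On timing, the abstract states: "These measurements are collected at baseline, 8 weeks, 5 months and 1 year after treatment". The Secondary outcomes section repeats this: "Assessments will be made at baseline and 8 weeks, 5 months and 1 year after treatment". The article describes no planned contact between the treatment visit and 8 weeks.

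Other information is also kept. The Intervention section says: "The use of pain medication besides the needling therapy is allowed and will be registered". Co-interventions are registered as well, and the paragraph on the 1-year contact adds that complications are registered.

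**The concern.** The plan expects a side effect that is temporary by its own description. It then relies on patients to mention it, or on staff to see it, with the first planned look 8 weeks later. A patient who was told to expect some worsening, and whose worsening has passed, has little reason to bring it up.

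What is at stake is the description of harms. The Study design section commits the report to the CONSORT statement, and adverse events are recorded, so a description of harms for the three injection treatments can be expected. If the count depends on who volunteers an event, the figure for the side effect the plan itself foresees will tend to be too low. This is a weakness in data collection; no analysis method is at fault.

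**Working it through.** The article gives no figure to reproduce, so the check sets the collection rule beside each route by which a flare could be recorded.

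1. **Does a short flare count as an adverse event?** Yes. The definition is broad enough, and temporary worsening is named as expected.

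2. **Treatment visit.** Staff can observe pain there, so injection pain on the day is covered. Worsening that starts later is not.

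3. **Spontaneous report.** It is open at any time, so capture is reduced and not zero. It depends on the patient's initiative.

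4. **Pain VAS at 8 weeks.** "Patients are asked to score their pain on this line during rest (at time of measure), provocation and maximum grip strength". These scores describe the elbow at the visit and would not show a flare that has settled.

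5. **Physical examination at 8 weeks (Table 1).** Range of motion, hydrops, pain on palpation, pain on resisted dorsiflexion and strength also describe the state on the day.

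6. **Questionnaires (Table 2).** Their recall periods are not given, and none is described as asking about worsening since the injection.

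7. **Complications, co-interventions and pain medication.** These are registered, but no method of asking about a flare is given. Medication use is at best an indirect marker.

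The gap is therefore a worsening that begins after the treatment visit, settles before 8 weeks and is not volunteered.

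**Size.** Three inputs would be needed: the true flare rate, how long flares last and the share volunteered. The article gives none of them. What follows from the planned 55 patients per arm (Sample size and power calculation) is only a unit: 1/55 = 0.018, so each missed flare lowers that arm's reported rate by 1.8 percentage points.

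To show how wide the possibilities are, assume a true rate of 20% to 60% and a captured share of 25% to 90%. Both ranges are assumptions with no basis in the document.

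- Flares per arm: 55 × 0.20 = 11 to 55 × 0.60 = 33.
- Recorded = 55 × rate × captured share: 11 × 0.25 = 2.75 to 33 × 0.90 = 29.7, about 3 to 30.
- Missed = 55 × rate × (1 − captured share): 11 × 0.10 = 1.1 to 33 × 0.75 = 24.75, about 1 to 25.

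The shortfall could be trivial or large. Its direction is clear; its size is not.

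**The case against.** The strongest reply is that the article condenses a fuller protocol. It places a duty on staff to record what is reported or seen, and it does not say that this is the only route or that staff refrain from asking. Prompts on the case report form and questionnaire recall periods commonly sit in the full document. Spontaneous reporting is also a legitimate and coherent way to collect adverse events, and the medication and co-intervention registers require information about the interval since treatment, where a notable flare may surface.

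Part of this stands. A fuller protocol may contain a prompt, and the registers may recover some events, which is why the conclusion is worded as probable and of unknown size. But the point rests on a collection method that the article states, set against a side effect and a visit schedule that it also states. It does not rest on silence alone.

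Three stronger readings are tempting, and the documents support none of them.

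- **Bias between arms.** A reader might infer that flares are missed unequally. The collection rule and schedule are the same in all arms, and patients and outcome assessors are blinded. The treating physician may be unblinded on the treatment day, but nothing shows that this leads to unequal recording.
- **Damage to the trial's conclusion.** Safety is not among the stated objectives, the Statistical analysis section names no comparison of adverse events, and the 5-month pain endpoint does not depend on them.
- **A size from the pilot or the calendar.** The pilot "concerning 25 patients treated with perforation therapy with the ITEC device reported no adverse device effects". The article does not say whether a flare counted as such an effect, so this shows neither that flares are rare nor how many go unreported. Likewise, the advice "to avoid lifting and heavy labor for one week" is a restriction on activity and not a flare duration, so counting days from it to the first visit measures no shortfall.

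**Conclusion.** The concern holds as a minor point about data collection. As described, a temporary worsening that settles before 8 weeks and is not volunteered will probably be under-counted in all three arms, by an amount that the document does not allow anyone to estimate. The consequence is confined to the descriptive report of harms.

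The conclusion assumes that the stated route is the main one in practice, that some flares resolve before 8 weeks, and that some patients do not mention them unprompted. If the full protocol already has staff ask about adverse events at follow-up, the point largely falls away.

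**What to change.** In the Adverse events section, add that adverse events are also asked for at each existing follow-up contact. At the 8-week visit, the blinded assessor asks every patient one fixed question: did your elbow pain get worse after the injection, and if so, for how many days?

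Ask it only after the VAS scores, physical examination and questionnaires are complete, because the 8-week VAS enters the mixed model and should not be coloured by the question. Report the answers descriptively by randomised arm, without a test, and state 8-week recall as a limitation. The visit comes before the 5-month crossover, so the answer refers to the randomised treatment.

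The cost is one item on an existing form at an existing visit. The downsides are recall error and a higher reported side-effect rate than spontaneous reporting would give. The result would be more complete and more evenly collected, but still not an exact rate. A call or diary in the first week would reduce recall error, but it adds staff work and is not asked for here.
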